# Efficacy and underlying mechanisms of *three-circle post standing qigong* on insomnia in college students: a four-arm, double-blind, randomized controlled trial protocol

**DOI:** 10.1186/s12906-024-04544-9

**Published:** 2024-06-18

**Keywords:** Insomnia, College students, Three-circle Post Standing Qigong, Randomized clinical trial, Therapeutic clinical effects and underlying mechanisms

## Abstract

**Background:**

Insomnia is common in college students, but its impact on health and wellbeing is often neglected. Enhancing sleep quality through targeted interventions could improve overall health and reduce the risk of consequent co-morbidities and mental health problems. Qigong exercises have been shown to significantly improve sleep quality and relieve insomnia. *Three-circle Post Standing* (TCPS) can help integrate body, breath, and mind, a fundamental principle of Qigong that promotes holistic wellbeing. In this clinical trial, we aim to (1) evaluate the feasibility, safety, and therapeutic efficacy of administering TCPS to improve sleep quality and quality of life in college students with insomnia; (2) explore the neurophysiological mechanisms underlying the mind adjustments mediated by TCPS in insomnia; (3) investigate body and breath pathophysiology mediated by TCPS in insomnia; and (4) assess the long-term efficacy of TCPS in terms of sleep quality and quality of life.

**Methods:**

This will be a prospective, parallel, four-arm, double-blind randomized controlled trial to investigate the effects and underlying mechanisms of TCPS on college students with insomnia. One hundred college students meeting diagnostic criteria for insomnia will be randomly assigned to receive either 14 weeks of standardized TCPS training (two weeks of centralized training followed by 12 weeks of supervised training) or sham-control *Post Standing* training. Efficacy outcomes including sleep quality, quality of life, neurophysiological assessments, plantar pressure, biomechanical balance, and physical measures will be collected at baseline, eight weeks (mid-point of supervised training), and 14 weeks (end of supervised training). Sleep quality and quality of life will also be evaluated during the four- and eight-week follow-up.

**Discussion:**

This trial will be an important milestone in the development of new therapeutic approaches for insomnia and should be easily implementable by college students with insomnia. The neuro- and pathophysiological assessments will provide new insights into the mechanisms underlying TCPS.

**Clinical trial registration:**

This trial has been registered in the China Clinical Trials Registry (registration number: ChiCTR2400080763).

## Introduction

College years are often a period of transition for students, marked by significant physical, psychological, and interpersonal changes and altered living and learning environments. Insomnia is common in many students during this period, with about a third of college students reporting getting less than seven hours of sleep per night and nearly two thirds describing poor sleep quality [1]. Similarly, in China, insomnia has been reported in 17% of college students [2]. College students with insomnia often complain that reduced sleep time and/or quality of sleep seriously affect their quality of life, daytime functioning, and academic performance, especially through fatigue, dizziness, headache, malaise, frequent mood lability, school absenteeism, and even accidents and injuries [3–5]. Furthermore, chronic insomnia can increase the risk of developing health problems such as obesity [6], diabetes [7], high blood pressure [7], coronary heart disease [8], and psychological disorders [3, 5] and exacerbate existing medical conditions and contribute to the development of suicidal thoughts [3, 9].

Most current clinical guidelines recommend short-term hypnotic medications for insomnia (up to 4 weeks) due to the risk of tolerance and dependence. These medications can cause notable side-effects such as hangover, morning grogginess, unusual sleep behaviors, memory/cognitive impairments, arrhythmia, fatigue, and rebound insomnia upon cessation [10, 11]. Cognitive behavioral therapy for insomnia (CBT-I) is recommended globally as first-line treatment for insomnia [10–12], but the high cost and a lack of trained therapists restrict access of CBT-I to many college students. In addition, adherence to and efficacy of CBT-I can be limited. A safe and effective mind–body intervention for insomnia is urgently needed for this population.

Qigong exercises are an important part of traditional Chinese medicine (TCM) that have attracted scientific and medical attention due to their potential mind–body health benefits [13, 14]. Recent high-quality randomized controlled trials (RCTs) and meta-analyses have demonstrated efficacy for Qigong exercises including *Tai Chi* [15], *Baduanjin* [16, 17], *Guolin Qigong* [18], and *Chan-chuang Qigong* [19] for effectively treating insomnia and significantly enhancing sleep quality. However, these Qigong exercises are all dynamic exercises incorporating the three fundamental “adjustments” of TCM Qigong theory—body, breath, and mind—where the goal is integrating these three elements and ultimately attaining a state of harmonious unity and holistic wellbeing [13, 14]. Beginners, especially those with poor coordination, may focus more on their movements rather than their breathing and mental states, and it often takes them longer to master dynamic exercises compared to static exercises in Qigong.

*Post Standing*, a static Qigong exercise, also known as "Zhan Zhuang", "standing stake", or "standing meditation", originated from the ancient Chinese proverb "stand alone and guard your spirit" found in "Plain Questions—On Health-Keeping of Remote Antiquity" or Su Wen—Shang Gu Tian Zhen Lun (素问·上古天真论). This ancient exercise is considered a fundamental posture and practice in various Qigong exercises. Over its long history, *Post Standing* has branched into various styles, where *Three-circle Post Standing* (TCPS) is a highly regarded and frequently practiced form of *Post Standing*. The salient characteristic of TCPS is the establishment of three distinct and interconnected circular configurations via the *Post Standing* stance, including the hand circle, which mimics the act of holding an open-fingered ball, the arm circle, which resembles grasping a tree, and the foot circle, which involves rotating the toes inward to create a semicircle [20]. During these exercises, abdominal breaths should be deep and regular [21], and the subject should concentrate on the three circular configurations with a relaxed demeanor [22]. TCPS can help practitioners achieve physical alignment and biomechanical balance that is more conducive to optimizing their exercises and integrating body, breath, and mind for harmonious unity.

Compared to pharmaceutical and psychological interventions, TCPS prioritizes holistic psychological wellness and emotional stability. It offers a proactive and self-practiced approach that allows individuals to regulate their own mind–body connection, unlocking their inner potential without constraints of time or space [22]. This makes TCPS a convenient and safe exercise for enhancing emotional stability, improving sleep health, and preventing psychosomatic disorders. However, there are currently few high-quality clinical studies of the effects of TCPS on insomnia. We have therefore designed a rigorous sham-controlled double-blind clinical trial with the primary objective of evaluating the efficacy of TCPS for treating insomnia in college students. Secondary objectives included assessing plantar pressure and biomechanical equilibrium, respiratory patterns, and resting-state brain activity in individuals engaging in TCPS. In conducting this comprehensive neurophysiological and pathophysiological analysis, we aim to evaluate whether individuals meet standards of TCPS and investigate the underlying mechanisms by which TCPS may impact insomnia.

This study aims to: (1) assess the feasibility, safety, and clinical efficacy of TCPS on sleep quality and quality of life in college students with insomnia in the sham-*Post Standing* controlled double-blind setting; (2) explore the neurophysiological mechanisms underlying the mind adjustments occurring in TCPS associated with insomnia by investigating the functional connectivity between brain regions through resting-state electroencephalography (EEG); (3) investigate the impact of body and breath adjustments in TCPS on the physical function of college students with insomnia by evaluating respiratory function, heart rate variability (HRV), blood pressure, and oxygen saturation; and (4) assess the long-term efficacy of TCPS in terms of sleep quality and quality of life.

Our primary hypothesis is that TCPS will improve sleep quality and quality of life of college students with insomnia compared with students engaging in sham-controlled *Post Standing* practice and that it will be safe, acceptable, and feasible. Our secondary hypotheses are that (i) the mind adjustment of TCPS will increase alpha and theta frequencies in specific brain regions, particularly in the alpha band, and enhance functional connectivity prior to observable improvements in sleep quality; and (ii) engaging in TCPS will modulate HRV, respiratory function, blood pressure, and oxygen saturation due to body and breath adjustments. Ultimately, we also expect TCPS to improve sleep quality and overall quality of life of students with insomnia following the intervention.

## Methods/design

This protocol was designed according to the Standard Protocol Items: Recommendations for Interventional Trials (SPIRIT) guidelines [23].

### Trial design

This will be a prospective, double-blinded, randomized controlled trial with a parallel four-arm design. Participants will be randomized to either TCPS or one of three sham-controlled *Post Standing* exercises. Participants and data collection/analysis personnel will be blinded to the intervention allocation.

### Study setting and procedure

All participants will be college students with insomnia admitted to the main campus (Shipai campus) of Jinan University, Guangzhou City, China. One hundred participants meeting the trial criteria will be included and randomly assigned to the standard TCPS group or three sham-controlled *Post Standing* groups according to a 1:1:1:1 allocation ratio with allocation concealment. The training regimen will include both centralized (two weeks) and supervised (12 weeks) training and a follow-up period of eight weeks, i.e., a total study duration of 22 weeks.

The primary outcomes will be measured using EEG data [24–27] and Pittsburgh Sleep Quality Index (PSQI) scores [28, 29] to evaluate central nervous system (CNS) bioelectrical activity and sleep quality, respectively. The secondary outcomes will include Insomnia Severity Index (ISI) scores [30, 31], 36-Item Short Form Health Survey Questionnaire (SF-36) scores [32, 33], plantar pressure and biomechanical equilibrium [34, 35], and physical function including respiratory function [36, 37], HRV [38, 39], blood pressure [40, 41], and blood oxygen saturation [42, 43].

All outcomes will be measured at baseline, at eight weeks (at the mid-point of supervised training), and at 14 weeks (at the end of supervised training). Sleep quality and quality of life will also be evaluated during the four- and eight-week follow-up periods. All measurements will be conducted in a professional exercise and human science laboratory. The study design is shown in Fig. 1 and the timetable is shown in Table 1.

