**Mechanism outcomes assessment**									
The bioelectrical activity generated by the CNS		**√**			**√**		**√**		
Plantar pressure and biomechanical balance		**√**			**√**		**√**		
Respiratory function		**√**			**√**		**√**		
HRV		**√**			**√**		**√**		
Blood pressure		**√**			**√**		**√**		
Blood oxygen saturation of blood		**√**			**√**		√		

*Abbreviations: CNS* central nervous system, *TCPS Three-circle Post Standing*, *PSQI* Pittsburgh Sleep Quality Index, *ISI* Insomnia Severity Index, *SF-36, 36*-Item Short Form Health Survey Questionnaire, *HRV* heart rate variability

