#### Neurophysiological assessment

A resting EEG is a graphical representation of the electrical activity of a group of brain cells. It is obtained by recording and amplifying the brain's spontaneous biopotentials from the scalp using advanced electronic equipment [24–27]. This study will use the Nuamps 40-channel EEG system and Curry 7 acquisition software (Compumedics, Charlotte, NC, United States). The sampling frequency will be set at 1000 Hz and the band-pass filter ranges from 0.01 to 100 Hz. EEG data will be preprocessed using the EEG MATLAB toolkit in MATLAB (R2012a, MathWorks, Natick, MA, United States). Power spectrum analysis will be used to measure the EEG, which quantifies the activity in different frequency bands of delta (2–4 Hz), theta (4–8 Hz), alpha1 (8–10.5 Hz), alpha2 (10.5–13 Hz), beta1 (13–20 Hz), beta2 (20–30 Hz), and gamma (30–40 Hz). The relative and absolute power levels of these frequency bands will be evaluated to assess brain activity and the basic neurophysiology of mind adjustment during TCPS. The study will also explore correlations within and between the hemispheres as well as the functional coupling between different brain areas to investigate the mechanisms underlying the effects of TCPS on insomnia.

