#### Statistical analysis

We will use IBM SPSS Statistics 25.0 (IBM Statistics, Armonk, NY) for statistical analysis, with a significance threshold of 0.05 and 95% confidence intervals for all estimates. Categorical variables will be reported as frequencies or percentages, while continuous variables will be described using mean ± standard deviation for normally distributed data and median [interquartile range (IQR)] for non-normally distributed data. We will conduct intention-to-treat (ITT) and per-protocol (PP) analyses for all outcomes. If ITT and PP results are consistent, we will consider them reliable; otherwise, ITT results will be preferred. For missing data, we will use multiple imputation and last observation carried forward analysis. Baseline demographic characteristics will be compared between groups using analysis of variance (ANOVA), non-parametric Wilcoxon signed rank, or chi-squared tests. Adjusted analysis with multiple linear regression or logistic regression will be performed if potential confounding factors are present. Repeated-measures ANOVA (group × time) will be conducted to compare outcome measures between the standardized TCPS and sham-controlled *Post Standing* groups and within the standardized TCPS group at different assessment time points. Safety will be assessed by recording and reporting adverse events for each group. A chi-squared or Fisher's exact test will be used to compare frequency differences in adverse events between groups, and severe adverse events will be described in detail. Logistic regression and linear mixed-effects models will be employed to explore factors affecting adherence and feasibility, adjusted for confounders. Adherence-related data will be obtained from training self-evaluation logs and sign-in sheets.

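### EEG is a primary outcome in the study procedure but secondary in the objectives and hypotheses, and as a primary it is a family of undefined variables with no rule linking it to PSQI

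*Protocol article*

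**What the plan says.** The protocol article gives EEG its status in several places.

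- **Study setting and procedure:** "The primary outcomes will be measured using EEG data" and PSQI scores. ISI, SF-36, plantar pressure and physical function are secondary.
- **Introduction, objectives:** the primary objective is the efficacy of TCPS for insomnia. Then: "Secondary objectives included assessing plantar pressure and biomechanical equilibrium, respiratory patterns, and resting-state brain activity in individuals engaging in TCPS".
- **Introduction, hypotheses:** the primary hypothesis concerns sleep quality and quality of life (with safety, acceptability and feasibility). EEG comes after it: "Our secondary hypotheses are that (i) the mind adjustment of TCPS will increase alpha and theta frequencies in specific brain regions", with emphasis on the alpha band.
- **Table 1:** "The bioelectrical activity generated by the CNS" stands under the mechanism heading; PSQI, ISI and SF-36 stand under the efficacy heading.
- **Sample size estimation:** an effect size of 0.31 for PSQI, four groups, three measurements, within-between interaction, 80% power and alpha 0.05 give 80 participants, raised to 100 for 20% attrition. EEG is not mentioned.
- **Neurophysiological assessment:** seven frequency bands. "The relative and absolute power levels of these frequency bands will be evaluated"; correlations within and between hemispheres and coupling between brain areas are to be explored as well.
- **Synchronous detection procedure:** recordings in three states (standing rest before practice, practice, standing rest after).
- **Statistical analysis:** group-by-time repeated-measures ANOVA "with a significance threshold of 0.05 and 95% confidence intervals for all estimates". It gives no rule for how the two primary outcomes combine.

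**The concern.** Which outcome is primary determines what the trial may claim, and the article answers in two ways. One primary outcome (EEG) appears only in a secondary hypothesis, while the primary hypothesis contains an outcome (quality of life, by SF-36) that is listed as secondary.

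The EEG primary is also named only as data. No band, power measure, region, recording state or time point is singled out. As the text stands, a null PSQI result could be reported beside a positive primary result on one EEG variable out of many, in a trial whose stated primary objective is efficacy for insomnia and whose size was justified on PSQI alone.

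**Working it through.** **1. Status, side by side**

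| Place | EEG | Quality of life (SF-36) |
|---|---|---|
| Study setting and procedure | primary, with PSQI | secondary |
| Introduction, objectives | secondary | not named in the primary objective |
| Introduction, hypotheses | secondary hypothesis (i) | in the primary hypothesis |
| Table 1 | mechanism | efficacy |
| Sample size estimation | not used | not used |

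The first row conflicts with the second and third on EEG, and with the third on quality of life. Table 1 fits a secondary reading of EEG but labels nothing primary or secondary, so it is supporting evidence only.

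**2. The plan's own sample size**

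Inputs: k = 4 groups, m = 3 measurements, f = 0.31, alpha 0.05. Degrees of freedom are (4 − 1)(3 − 1) = 6 and (80 − 4)(3 − 1) = 152. With the effect size specified as in SPSS, the noncentrality is

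λ = f²(N − k)(m − 1) = 0.0961 × 76 × 2 = 14.61,

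which gives power 0.813 at N = 80. N = 76 gives 0.787, so 80 is the smallest multiple of four that reaches 80%. Attrition: 80 / (1 − 0.20) = 100. The stated 80 and 100 are reproduced, for one PSQI test at 0.05. The convention matters: the G*Power default, λ = f²Nm/(1 − ρ) with ρ = 0.5, would give N = 28. I use the convention that reproduces the plan.

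**3. Size of the EEG family**

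- 7 bands × 2 power measures = 14 variables.
- 14 × 3 recording states = 42 variables.
- Regions and connectivity would add to this, by a number that the article does not give.
- Narrow reading, limited to the bands in secondary hypothesis (i): theta, alpha1 and alpha2 × 2 power measures = 6 variables, in one state.

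**4. Chance of at least one p < 0.05 when nothing differs, if any one variable counts**

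Independent tests: 1 − 0.95^n, where n is the number of tests. So 1 − 0.95^14 = 0.512 and 1 − 0.95^42 = 0.884.

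Correlated tests, with a common correlation r between two-sided z statistics and c = 1.96:

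1 − ∫ φ(u) [Φ((c − √r·u)/√(1 − r)) − Φ((−c − √r·u)/√(1 − r))]^n du

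The article gives no correlation, so r is an assumption and is shown as a range.

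| Tests | r = 0 | 0.3 | 0.5 | 0.7 | 0.9 |
|---|---|---|---|---|---|
| 6 | 26.5% | 24.1% | 20.7% | 16.4% | 10.8% |
| 14 | 51.2% | 43.8% | 34.8% | 24.9% | 14.1% |
| 42 | 88.4% | 75.9% | 58.3% | 38.2% | 18.6% |

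**5. Cost of keeping two primaries**

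Suppose one pre-named EEG variable and PSQI are each tested at 0.05, and either may succeed. The overall error is then 1 − 0.95² = 9.75% if they are independent. Splitting alpha at 0.025 each holds the total at 0.05 or below, but power for PSQI at N = 80 falls from 0.813 to 0.727. The required N rises to 92 (power 0.809; N = 88 gives 0.784). With 20% attrition that is 92 / 0.80 = 115, or 116 for equal arms, against the planned 100.

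**The case against.** A reader might infer that a false-positive primary result is likely. The article does not support that. It needs a rule that any one significant EEG variable is enough, which is not stated (nor is a rule that EEG and PSQI must both succeed). It also needs fairly weak correlation. Relative powers are shares of one total, absolute and relative power in a band come from the same data, and the three states come from one person in one 3 + 5 + 3 minute sequence, so high correlation is plausible. At r = 0.7 the figures are 25% and 38%, and at 0.9 they are 14% and 19%. This objection stands.

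A reader might also infer that the EEG tests will go uncorrected. The article states no correction, but that is not a statement that none will be made. An analysis plan that is not shown could contain one. This stands too, and the absence of a multiplicity procedure is not the point raised here. No such plan would remove the conflict inside the article over which outcomes are primary.

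Nor is it right that the trial has no error control at all. The PSQI test keeps its own 0.05 level whatever the size of the EEG family.

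Finally, the connectivity work is worded as exploratory and the hypothesis narrows to alpha and theta. That reduces the family, but even six variables stay above 5% at every correlation considered, and the primary-outcome sentence does not adopt the narrowing.

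**Conclusion.** The concern holds as an inconsistency with a consequence. EEG is primary in one section and secondary in the objectives and hypotheses; quality of life is in the primary hypothesis but secondary as an outcome; and only PSQI was used to size the trial. The EEG primary is undefined among at least 14 named variables, or 42 across recording states.

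If any one EEG variable were allowed to count, the false-positive chance would lie between 14% and 51% for 14 tests, and between 19% and 88% for 42, as the assumed common correlation runs from 0.9 to 0. These figures are conditional on that reading and on those correlations. The status conflict depends on neither and should be resolved before any data are analysed.

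**What to change.** - **Study setting and procedure:** make PSQI the sole primary outcome, tested by the group-by-time analysis over three measurements that the sample size was built on. Move EEG to the secondary or mechanistic outcomes, in line with the objectives and hypotheses.
- **Introduction:** take quality of life out of the primary hypothesis, so that SF-36 is secondary in both places.
- **If a key EEG measure is wanted:** name one sub-band, power type, region, recording state and time point. The hypotheses emphasise alpha, but that alone leaves 2 alpha sub-bands × 2 power types × 2 resting recordings = 8 candidates before region and time point. Apply false-discovery-rate control to the other EEG measures, or label them exploratory.

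**Cost.** This is a change of protocol wording, and of the registry entry if that repeats the same text. Procedures and recruitment are unaffected. EEG loses primary status. If the sponsor prefers to keep a single named EEG variable as a second primary with alpha split, the price is the power loss to 0.73 at N = 80, or 92 analysed participants, shown above.

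Replacing the group-by-time test with a comparison at week 14 alone would not be a mere wording change. If the same f = 0.31 is assumed for a one-way, four-group comparison, λ = 0.0961 × 80 = 7.69 gives power of about 0.61 at N = 80. About 120 analysed participants would be needed for 80%, before any gain from baseline adjustment.
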